**6.14 Group Information**

There will be two arms or groups of information in the selected districts of the zone. There will be an intervention group (who receive couples-based violence prevention education) and a control group (who receive usual care). Hence, the clusters will be assigned into two arms by randomization. An intensive health education message will be delivered to the intervention arms based on the baseline findings. The type of unit under this study will be clusters. The four selected districts have a total of 116 clusters. Out of 49 eligible clusters, 16 clusters will be selected by simple random sampling. In each cluster, there might be 27 couples (husbands and pregnant wives) who have the potential for the health education message. Therefore, an intervention arm consists of 8 clusters, and a control arm consists of 8 clusters. There will be 27 couples per cluster, forming a total of 216 couples (216 male partners and 216 pregnant wives) in the intervention group and 216 in the control group, making 432 couples, which will be followed in the intervention period.

**6.15 Description of the Intervention**

The purpose of the study is to provide community-based health education to couples on violence prevention to reduce intimate partner violence during pregnancy. A group health education on violence prevention, including intimate partner violence, for couples in the intervention group will be provided in a place center for the participants. 16 kebels found in the four districts will be the study clusters.

A package of health education messages on violence prevention will be provided to couples living in the intervention arm. The package was adapted from a psychosocial education study conducted among couples (Mutisya et al., 2018) and gender transpormative education on intimate partner violence in Tanzania (Harvey et al., 2021). The health education messages will be conducted by health extension workers who are working in intervention clusters (kebeles). Eight health extension workers will be selected for the intervention (CBVP education). The following criteria will be used to recruit health extension workers:

- Health Extension Workers who are female
- able to speak Amharic and the local language (Hadiyisa).
- willing to participate in the study period
- Good interpersonal and communication skills
- Having participated in a survey previously

**Consort Diagram**

The study protocol containing the detailed information is depicted in the consort diagram below (Figure 5).

116 rural kebeles found in Soro,Lemo, Analemo and Duna Districs

49 eligible kebeles

16 kebeles selected

Randomization of 16 kebeles (intervention and control arms)

Allocation

Intervention arm (8 clusters)

Control arm (8 clusters)

Participants will be assessed for eligibility criteria

 Participants will be assessed for eligibility criteria

Enrollment

Informed consent and

Baseline data collection

Informed consent and

Baseline data collection

Intervention group receive

CBVPE

Control group continue to receive routine care

Analysis

8 months follow-up survey

Intervention

Identification of couples whose wife is pregnant

Figure 5: Consort flow diagram

**6.15.1 Couple education contents and sessions**

**Control group (study group 1):** no intervention will be provided for these clusters (kebeles) from the research group. However, the control group will not be restricted from the standard health extension package services provided by health extension workers.

**Couples GBV prevention education group (study group 2):** in this group, the couples (pregnant women and their male partners) will be educated on:

- Gender-based violence
- Violence against women
- Intimate partner violence
- Types of intimate partner violence (physical, sexual, and psychological or emotional violence)
- Magnitude of intimate partner violence in pregnancy
- Inequitable gender norms and consequences
- The relationship between intimate partner violence and power and control
- Common triggers of IPV in pregnancy
- Uhhealthy and healthy relationship
- Common triggers of IPV and ways to challenge the triggers
- Effective communication and conflict resolution in relationship

The couple’s education will be provided every fourth week by the health extension workers, assisted by the researcher. Baseline data will be collected from 10 to 12 weeks of gestation. The education services will be provided in groups, and each participant has six contacts with the educator. The contents and sessions for couple education are illustrated below in Figure 7.

**1^st^ session**

13-16 weeks gestatio

- Gender based violence (what is it)
- Violence against women (what is it)
- Intimate partner violence (what is it )
- Types of IPV
- Physical, sexual and psychological
- Magnitude of intimate partner violence

Schedule by weeks

Content ofcouple based violence prevention education

- Adverse maternal and newborn consequences of IPV during pregnancy
- Economic and social consequences of IPV during pregnancy
- Common triggers of IP
- Ways to challenge triggers of IPV

**2^nd^ session**

17-20 weeks

- Healthy and unhealthy behaviors in marital relationship
- Important characteristics of healthy relationships

**3rd session**

21-24 weeks

- Common gender norms for women and men
- Gender and sex
- Inequality gender norms related to IPV during pregnancy
- The ways to challenge inequitable gender norms

**4^th^ session**

25-28 weeks

- Effective communication skills in relationship
- Nonviolent ways of conflict resolution in relationship

**5^th^ session**

29-32 weeks

- Define power and control
- Healthy power balance within relationship
- Benefits of joint decision making
- Seven strategies to joint decision making

**6^th^ session**

33-36 weeks

Figure 6: the schedule for couples education and message contents of intervention group

**6.15.2 Description of education sessions**

**Control group (study group 1):** participants in the control clusters receive routine standard care from the health extension workers**.** Education on violence prevention, including intimate partner violence, will not be provided by the research team. This group will simply receive the health extension package services provided by HEWs.

**Intervention group (study group 2)**: Pregnant women and their husbands will receive couple-based violence prevention education (CBVPE) from the 13–16 weeks of gestation to delivery for six months. The intervention package is aimed at raising knowledge and awareness of gender-based violence, types of intimate partner violence, adverse maternal and new-born outcomes of IPV during pregnancy, common triggers of intimate partner violence during pregnancy and its management, a healthy relationship in marriage, communication, and problem-solving skills. After adequate training, HEWs will provide health education to couples in the intervention arms at the health post in groups. It will be provided every month for six consecutive times. Each session may take 50-60 minutes. All sessions will contain interactive lectures, take-home exercises, and reflection. During class sessions, flip chart paper and posters will be used. It is designed with the intention that they will be carried out in an enclosed workshop space. Neither the HEWs nor the participants will be informed about the intervention hypothesis.

**6.15.3 Intervention fidelity**

Intervention fidelity refers to the degree to which components of intervention are executed as designed. To enhance the intervention's fidelity, we will implement the following actions: a trainer manual has already developed; extensive training will be provided for interventionists (HEWs); spot checks will be conducted by field supervisors during each intervention session; and feedback meetings with interventionists will be held after each session. A fidelity checklist that addresses adherence and intensity of the intervention will be used to evaluate intervention fidelity at the end of each session.

Table 2:summary of the intervention package and implementation process

| **Session** | **Content of the message** | **Dose** | **Strategy of delivery** | **Frequency** | **Compliance parameters** | **Responsible person** |
| --- | --- | --- | --- | --- | --- | --- |
| Session 1  (13-16 weeks) | - Introducing each other - Gender based violence (what is it) - Violence against women(what is it) - Intimate partner violence(what is it ) - Types of intimate partner violence - Physical, sexual and psychological - Magnitude of IPV - Summarization - Introduction on take home-exercise next - Appointment to next session | 60 minutes | • Brain storming • Lecture • Question and Answer  **.**Take-home exercise and reflections | Once | -% couples participated | Researcher, Supervisors & Health extension workers |
| Session 2  (17-20 weeks) | - Refelection on take home exercise and recap - Maternal and new born consequences of IPV - Economic and social consequences - Family and dependents consequences - Common triggers of IPV during pregnancy - Ways to challenge triggers of IPV - Introduction on take-home exercise - appointment to next session | 60 minutes | • Brain storming • Lecture • Question and Answer  **.**Take-home exercise and reflections | Once | -% -% couples participated | Researcher, Supervisors & Health extension workers |
| Session 3  21-24 weeks | - Reflection on take home exercise - Common gender norms for women and men - Gender and sex - Inequality gender norms related to IPV during pregnancy - The ways to challenge inequitable gender norms - Introduction on take-home exercise and appointment to next session | 60 minutes | • Brain storming • Lecture • Question and Answer  **.**Take-home exercise and reflections | Once | -% -% couples participated | Researcher, Supervisors & Health extension workers |
| Session 4  (25-28 weeks) | - Recap and reflection on take home exercise - Healthy and unhealthy behaviors in marital relationship - Important characteristics of healthy relationships - Introduction on take-home exercise and appointment to next session | 55 minutes | • Brain storming • Lecture • Question and Answer  **.**Take-home exercise and reflections | Once | -% -% couples participated | Researcher, Supervisors & Health extension workers |
| Session 5  (29-32 weeks) | - Recap and Reflection on take-home exercise - Define power and control - Healthy power balance within relationship - Benefits of joint decision making - Seven strategies to joint decision making - Take | 60 minutes | • Brain storming • Lecture • Question and Answer  **.**Take-home exercise and reflections | Once | -% couples participated | Researcher, Supervisors & Health extension workers |
| Session 6  33-36 | - Recap and reflection on take home exercise - Effective communication skills in relationship - Nonviolent ways of conflict resolution in relationship   Summarization and close up | 60 minutes | • Brain storming • Lecture • Question and Answer | Once | -% couples participated | Researcher, Supervisors & Health extension workers |
|  | Provision of printed take-home materials | -Poster | - | Delivered during in each training session | -% of couples received posters | Researcher, Supervisors & Health extension workers |
|  | **End line data collection** | - | - | at 8^th^ month of intervention | % pregnant mother and their husbands interviewed | Researcher, supervisors and data collectors |

**6.15.3 Appointment and follow-up for intervention group**

The contact address of each couple included in the study will be taken. The addresses of the couples, including kebele, gote (sub-kebele), house number (if applicable), and telephone number, will be taken by the researcher and the HEWs (educators). At the end of each session, the educator and the participant will agree on the date of the next visit, which will be recorded by the educator in her diary and on a similar diary that will be left with the participants. Before the next visit, the educator reminds the couples about the next session by calling or messaging them. Either of the couples who missed the classroom sessions will be visited by HEWs at their home to rule out the reason for their absence. Then another classroom session will be arranged. At the end of each session, the number of couples who attended will be recorded. Couples in the intervention clusters will be visited three times in case of absence to improve the participants’ compliance. End-line data collection will be carried out at month 8. Every month, HEWs will screen the couples for any dispute or disagreement during a home visit by asking either of the couples if there is any disagreement or dispute due to intervention. If so, she negotiates with the couples. If the dispute still continues in the second screening, she communicates with the principal investigator, and they both resolve the dispute between the couples as much as possible.

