## Studies found that women who reported intimate partner violence were significantly associated with intrauterine retardation and pre-mature labor (Martin-de-Las-Heras et al., 2019; Yu et al., 2018). Women who experience intimate partner violence during pregnancy also found that increased women’s risk of miscarriage and abortion (Afiaz et al., 2020; Alhusen et al., 2015). Intimate partner violence during pregnancy is also associated with a higher risk of antepartum and postpartum depression, anxiety, suicidal attempts, a lack of attachment to the child, and a lower level of breast feeding (Alhusen et al., 2015; Bonomi et al., 2009; Martin-de-Las-Heras et al., 2019; WHO, 2011a). Intimate partner violence is considered a tip of the iceberg, or silent epidemic, since many victims do not reveal their experience of violence from an intimate partner due to barriers (Palermo et al., 2014). Intimate partner violence has a spill-over effect. It affects not only the women and the newborns but also the family, community, society, and the nation at large (Jill Ryan and Roman, 2019).1.2 Statement of the problem

Violence against women is a phenomenon that occurs in all countries around the world (WHO, 2011b). Violence against women has been an important public health, social policy, and human rights concern since the 1993 World Conference on Human Rights and the Declaration on the Elimination of Violence against Women (UN, 1993). The majority of violence against women is committed by an intimate partner. Each year, between 1.5 and 5.3 million women are physically and/or sexually assaulted by an intimate partner (K. M. Devries et al., 2013). In the WHO multi-country study on women’s health and domestic violence against women, it was found that the prevalence of physical intimate violence in pregnancy was one percent in Japan and 28% in Peru (WHO, 2010). According to the analysis of Demography and Health Surveys and the International Violence against Women Report, the prevalence of intimate partner violence during pregnancy is lowest (2%) in Australia, Denmark, Cambodia, and the Philippines, and highest (13.5%) in Uganda. A review of clinical studies from Africa reported in 2011 showed prevalence rates of 23–40% for physical, 3–27% for sexual, and 25–49% for emotional intimate partner violence during pregnancy (Shamu et al., 2011).

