**5.10 Operational Definition**

**Couple**: a man and woman living together, whether married or not.

**Intimate partner**: a current husband or cohabiting partner (living in the same house without formal marriage)

**Intimate partner violence**: pregnant women who reported any violence in the form of physical, psychological, or sexual violence, or any combination of the three, by their husband during pregnancy (Trott et al., 2017).

**Physical violence** refers to when a pregnant woman reports one or more acts of slapping or throwing something at her that could hurt her, pushing, shoveling, or pulling her hair, hitting her with her fist or with something else that could hurt her, kicking, dragging, or beating her up, attempting to choke or burn her on purpose, and threatening to use or actually use a gun, knife, or other weapon during the most recent pregnancy (WHO, 2010).

**Sexual violence:** refers when pregnant women reports that they experience one or more physically forced her to have sexual intercourse with him when she did not want to, forced her with threats or in any other way to perform sexual acts she did not want and physically forced to perform any other sexual acts she did not want toduring the most recent pregnancy (WHO, 2010)

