**6.18 Data Collectors**

**Data collectors for quantitative study:** 10 diploma-level female nurses will be selected to collect data from the respondents as recommended by WHO to enhance the disclosure of IPVp (WHO, 2007). Data collectors will be trained by the researcher for three days. The selection criteria include:

- Certified diploma female nurses
- Able to fluently speak Amharic and the local language (Hadiyisa).
- Having good interpersonal and communication skills.
- Willing to collect data at the baseline and end of the study

**Data collectors for the qualitative study**: two female moderators will be selected to facilitate FGD. The moderators will be female master’s holders in public health, and those with previous experience in qualitative data collection will be recruited. The same number and criteria as the FGD moderators will be used for the in-depth interview (IDI). The recruitment for the FGD moderators and IDI (interviewers) includes the following criteria: having a master’s degree in the area of public health, being able to speak Amharic and local languages (Hadiyisa), and having previous experience in qualitative data collection.

**Supervisors for quantitative study**: Two supervisors will be recruited for quantitative data collection. When recruiting the supervisor, a master’s degree in a related field and, preferably, previous supervision experience will be used. Their role in the field includes: monitoring health educators and data collectors; making sure education is properly implemented; helping educators and data collectors with any challenges faced during field work; and informing the researcher of any concerns.

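### The monthly check for disputes caused by the intervention can be met by asking the husband alone, and its negotiate-first response makes no exception for violence

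*Protocol*

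**What the plan says.** The rule is in the Protocol, section 6.15.3, Appointment and follow-up for intervention group. It opens: "Every month, HEWs will screen the couples for any dispute or disagreement during a home visit". The check is made "by asking either of the couples if there is any disagreement or dispute due to intervention. If so, she negotiates with the couples". Escalation follows: "If the dispute still continues in the second screening, she communicates with the principal investigator, and they both resolve the dispute between the couples", as far as they can.

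Other parts of the Protocol bear on it:

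- Section 1.1 (Background) says that "many victims do not reveal their experience of violence from an intimate partner due to barriers".
- Section 6.18 (Data Collectors) protects disclosure in the surveys: "10 diploma-level female nurses will be selected to collect data from the respondents as recommended by WHO to enhance the disclosure of IPVp". The Ethical Consideration section makes interviews private, with the respondent choosing where and when.
- Section 5.10 (Operational Definition) defines partner violence as physical, sexual or psychological violence by the husband. The physical acts include "attempting to choke or burn her on purpose, and threatening to use or actually use a gun, knife, or other weapon".
- Section 6.15.3 (Intervention fidelity) says that "feedback meetings with interventionists will be held after each session". Section 6.18 gives supervisors the duty of "informing the researcher of any concerns". Section 6.15.1 has the researcher assist the educators, and Table 2 lists the researcher among those responsible for every session.

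**The concern.** This is a trial of partner violence in which the husband is, by definition, the possible perpetrator. The monthly home check is the one step in the available text that both looks for trouble in an individual couple and says what to do about it. An educator can follow it exactly by asking the husband, or by asking the wife while he listens. If trouble is reported, the instruction is to negotiate with both partners, whatever form the trouble took.

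What is at stake is the safety of women in the intervention arm, not the effect estimate. The Protocol takes care over disclosure when it measures the outcome and does not carry that care over to the check meant to catch harm from its own sessions.

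**Working it through.** This is a reading of the text; the Protocol gives no figure to reproduce. Each element of the rule is set against the passages that might qualify it.

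**Who answers.** The rule accepts either member of the couple. The same paragraph uses the same expression for a partner who missed a session, where it plainly means one spouse. One answer is enough, and it may be the husband's. The privacy promise under Ethical Consideration concerns interviews. Even if it is extended to these visits, it does not say which spouse is asked.

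**What is in scope.** The opening words are general, but the question that carries out the check concerns disputes caused by the intervention. That is a workable scope for a harm check, and it is taken as the scope here.

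**What follows a positive answer.** Negotiation with the couple is the only first response stated. Investigator contact falls due at the second screening if the dispute continues. Screening is monthly, so the interval from first positive answer to required contact is 1 screening interval, about 1 month. The paragraph does not mention violence, so nothing separates a quarrel over a take-home exercise from an act listed in section 5.10.

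**Other channels.** The researcher's part in sessions, the feedback meetings and the supervisors' duty all allow a case to be raised sooner. None of them says that a violent act must be raised. The training list for health extension workers in section 6.19 names neither handling of a disclosure nor referral; interviewing skills and research ethics are listed there for data collectors only. The Ethical Consideration section and the trainer manual contain no response path for violence.

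**Coverage.** Section 6.14: 8 clusters x 27 couples = 216 couples. Section 6.11 gives 213, which changes nothing here.

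**Context.** Section 6.8 plans on 37.5% prevalence of partner violence in pregnancy: 0.375 x 216 = 81 women. With the planned 20% decline read as relative, 0.375 x 0.80 = 0.30, and 0.30 x 216 = 64.8, about 65. Read as absolute, 0.375 - 0.20 = 0.175, and 0.175 x 216 = 37.8, about 38. These are women with any form of violence. They are not disputes caused by the intervention, and they are not women missed. They show only that, on the Protocol's own assumptions, educators will be visiting affected households.

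**The case against.** The strongest reply is that the check is narrow by design. It looks for trouble that the education causes, and a violent act reaches the negotiation step only if it is reported as such a dispute. That stands, and it limits the point to intervention-related disputes. It does not answer who is asked or what happens when such a dispute has turned violent.

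A reader might infer that the sentence contradicts itself, screening for any dispute but asking only about those the intervention caused. The text does not support this: the second clause specifies how the check is done and so sets its scope. Widening the question while keeping the negotiation step would also add general marital mediation to one arm and change the intervention under test.

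A second reply is that the researcher is never far away: assisting at sessions, holding feedback meetings and hearing from supervisors. That also stands. About a month is the latest date at which contact falls due, not an expected delay, and nothing forbids raising a case at once. But nothing shown requires it.

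A reader might also infer that the trial has no response to violence at all. The available text cannot establish that. Some pages, consent pages among them, are missing from it, and a referral path could be there. Such a path would still leave the instruction in 6.15.3 reading as it does.

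**Conclusion.** The point holds as a participant-safety defect in a stated field rule. The monthly check can be satisfied by the husband's answer without privacy. An intervention-related dispute involving violence as defined in section 5.10 would be negotiated jointly, with investigator contact not required for about a month. It applies to all 216 intervention couples. It rests on the plain reading of the paragraph, on monthly screening, and on the available text containing no overriding rule.

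The size in women cannot be given. The Protocol has no rate for which spouse answers, how often the sessions provoke disputes, or how often those turn violent. A reader might infer long undetected harm: from a first check at month 1 to the endline at month 8 is 8 - 1 = 7 months. That would require every check in between to miss, and nothing in the Protocol says how likely that is. Nor does the defect alter the effect estimate, the power or the analysis. It is a cheap improvement that should be made.

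**What to change.** Amend the paragraph in section 6.15.3 (Appointment and follow-up) in two places:

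1. The educator asks the woman herself, alone and out of her husband's hearing.
2. Any reported act of violence as defined in section 5.10 is not negotiated with the couple and does not wait for a second screening. It is passed promptly, with the woman's agreement and in confidence, to the principal investigator, for a response approved by the ethics board before the first session.

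Keep the restriction to disputes caused by the intervention, and keep the existing negotiation path for non-violent disputes.

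**Cost.** The home visits are already planned and section 6.15 already requires female educators. With 8 educators for 216 couples, each makes 216 / 8 = 27 visits a month. At an assumed 3 to 5 extra minutes per visit, that is 27 x 3 = 81 to 27 x 5 = 135 minutes per educator per month, for the private question only. The three-day educator training needs a short addition, and the response path must be written and approved.

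**Downside.** Private questioning in one arm only may change how readily women disclose violence at endline, and the primary outcome is self-reported. A brief question reduces this without removing it; report it as a limitation. Control-arm women have no monthly check under either wording.
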